## Abstract

**Background:**

Health literacy is a critically important skill that helps people become active participants in their health care. Multiple studies in the United States and across the world have documented the association of health literacy with multiple health outcomes. In particular, the elderly and many members of minority groups have been shown to have low levels of health literacy; the same groups are disproportionately affected by chronic illnesses. These twin burdens affect the people most in need of the skills and knowledge required for coping with chronic illnesses. Chronic disease self-management (CDSM) is a logical target for a general health literacy intervention. In an approach that spans across specific diseases, CDSM targets problems and skills needed to cope with issues such as fatigue, pain, stress, depression, sleep disturbance, and treatment adherence. In a previous study, we showed that a computer-delivered tailored information intervention targeting health literacy could improve treatment and adherence and be cost effective, but it is not clear that this same strategy will be effective in persons with low health literacy and multiple chronic conditions.

**Objective:**

The purpose of this study is to develop a computer-delivered mobile intervention that will provide individuals with chronic conditions the necessary information to cope with their conditions.

**Methods:**

In this project, we will complete a qualitative study on the status and needs of individuals with more than one chronic condition. Results of this study will be used to develop a mobile tailored information app that will address self-management challenges in the areas of pain, sleep, fatigue, depression, anger, stress, memory problems, and treatment adherence. The impact of the intervention on patient quality of life, patient-provider relationships, health literacy, and patient activation will be assessed. We will also explore the extent to which health literacy mediates important outcomes, such as health-related quality of life and health service utilization.

**Results:**

We are currently completing the preliminary qualitative and usability studies that will inform the content and design of the intervention. We anticipate that the intervention will be complete in 2017, and the clinical trial of its efficacy will also commence in 2017.

**Conclusions:**

Results will provide evidence on the usefulness of a mobile tailored information app for improving health literacy, patient activation, health-related quality of life, and self-reported health in patients with multiple chronic conditions.

**Trial Registration:**

Clinicaltrials.gov NCT02922439; https://clinicaltrials.gov/ct2/show/NCT02922439 (Archived by WebCite at http://www.webcitation.org/6pTiqDAyN)

## Introduction

### Low Health Literacy and Disparities

Health literacy is a critically important ability that is a key route by which people can become active participants in their health care. The 2003 National Assessment of Adult Literacy in the United States showed that more than 75 million Americans had, at best, only basic health literacy skills, suggesting that as many as 1 in 4 are unable to understand the complexities of health care [1]. The importance of health literacy is underscored by multiple studies that have linked levels of health literacy to health status and outcomes [2-4] that even include risk of death [5,6]. Persons in racial/ethnic minorities and the elderly are even more likely to have low levels of health literacy. Twenty-four percent of blacks (9.5 million persons), 41% of Hispanics (21 million persons), and 29% of persons 65 years of age or older (12.5 million persons) have below-basic levels of health literacy [1], suggesting that they may be unable to use health information for even the most basic tasks, such as following simple directions on how to take a medicine. The ability to effectively obtain, interpret, and use relevant information to maintain health and cope with illness is increasingly important in today’s complex health care system, in which patients are required to take more responsibility for their care [7]. Further highlighting the importance of health literacy, compelling evidence links race and age to health via health literacy [3,8-12]. In the proposed study, we will assess the potential moderating effect of race, ethnicity, and age in response to an intervention to improve health literacy (Aim 3, discussed below).

### Need for Downstream Interventions Targeting Disparities

While the causes of health disparities are broad, complex, and rooted in social, cultural, and economic factors [13,14], health care services are still delivered to at-risk individuals every day. An urgent need exists for *downstream* interventions that can affect health disparities at the point of care [15]. Interventions that improve patients’ ability to manage their own health care may be especially critical given ongoing changes in the US health care system, which requires patients to take greater responsibility for their personal and family health care decisions [7,16,17], even as the system becomes more complex for underserved minorities [18] and the elderly [19]. Provisions of the Affordable Care Act in the United States, for example, specifically promote shared decision-making and the development of patient decision-making aids [20] to address these issues.

### Multimorbidity and Chronic Disease Self-Management

Chronic disease self-management (CDSM) is a logical target for a downstream intervention to address disparities and low health literacy. CDSM skills involve a wide variety of strategies that can be implemented by patients themselves to cope with chronic conditions. These strategies can include, for example, cognitive techniques for managing chronic pain (eg, distraction, reframing) or behavioral techniques (eg, graded exercise for fatigue and shortness of breath). While specific health conditions may require disease-related management skills (eg, glucometer use in diabetes), common issues such as fatigue, depression, stress, sleep disturbance, and treatment adherence span across illnesses and can be addressed in a single intervention; several of these have been the focus of a previously developed in-person group-delivered CDSM intervention [21-24]. In this continuation of our research on health literacy, we will expand on other interventions by first completing a qualitative study to inform the development of a general CDSM intervention. We will use the measure of health literacy created in an earlier study [25-27] to evaluate participants’ levels of health literacy and provide them with a version of the intervention tailored to their level of health literacy, preferred language, and race or ethnicity. In the proposed study, we will evaluate the effectiveness of a tailored intervention to improve health literacy (Aim 2, discussed more extensively below).

### Chronic Disease Self-Management and Health Literacy

CDSM integrates well with our previously developed and validated model of health literacy [26]. In the Abilities-Skills-Knowledge (ASK) model of health literacy, we argue that health literacy performances (such as finding and acting upon information about a disease) depend on general cognitive abilities (verbal reasoning, attention, working memory), specific skills (eg, reading and listening comprehension), and disease-related knowledge [26]. While efforts to improve basic cognitive abilities have been met with limited success, it is clear that patients can learn specific skills that will facilitate their understanding of oral and written health information, and can also learn conceptual knowledge about diseases. Created prior to the explicit formulation of the ASK model, the intervention targeting health literacy in persons treated for human immunodeficiency virus (HIV) [28-30] followed its principles and demonstrated the effectiveness of the instructional strategies discussed below. In this study, participants showed improvements in disease-related information and medication adherence [30]. An important finding in this study was that race-related differences in disease information were no longer significant after black participants completed the intervention [30]. In the project discussed in this paper, we will draw on this experience, as well as our current pilot study of an ASK model-based intervention for diabetes, in creating an efficacious intervention to improve health literacy in individuals with multiple chronic health conditions.

An alternate strategy to provide patients with the skills and knowledge to understand and manage their health is also important, because the dominant format for information delivery to patients in clinical care is oral communications during brief (and often rushed) clinical encounters [31]. Patient learning in these contexts is often suboptimal, at levels substantially less than 50% of the material presented [32], and during these encounters providers often fail to provide key information [33,34]. Unfortunately, it may be difficult or impossible to help patients develop self-management skills if they do not have basic health-related reading and math skills or health-related knowledge. Health literacy is likely to be an essential aspect of developing CDSM skills.

The ASK model will be the explicit basis for the development of our mobile app. We will first complete a qualitative study to better understand the skills and knowledge needs of individuals with both self-management needs and low health literacy. Results of this qualitative study will inform the development of the intervention. The ASK model will provide a general framework for the content of the intervention, while the results of the qualitative study will provide a guide to its content.

### Health Literacy Interventions

The previously developed conceptual model of health literacy [26] states that health literacy, after considering demographic variables, comprises basic cognitive *abilities*, relevant academic *skills*
**,** and health care-related conceptual *knowledge* (ASK). An advantage of this model is that it leads directly to interventions. While it may be difficult to change patients’ basic cognitive abilities, interventions can readily be developed to improve patients’ skills at acquiring and understanding health information, along with their knowledge of health conditions and treatment. Strategies used in previous studies to improve patients’ health literacy have included providing information, improving skills (eg, reading comprehension), and targeting psychosocial constructs (eg, self-efficacy or patient activation) [3]. Reviews of these studies suggest that while some strategies were useful, no clear consensus on methods, content, or their effectiveness has emerged [3,8,35,36]. Expert recommendations for health literacy interventions include rejecting a *one size fits all* approach [37], creating interventions that promote participant engagement and retention through interactivity and interesting multimedia elements, and ensuring learning through an interactive teach-evaluate-reteach algorithm when needed [29,30,38,39]. The planned project will follow these recommendations in creating a tailored, interactive, and multimedia intervention to improve CDSM skills in participants with low levels of health literacy.

Tailoring content to make interventions more personally relevant and appropriate to patients’ levels of health literacy has been advocated as an effective strategy for health communication [40-42]. Tailoring can promote engagement and facilitate behavior change, as previously demonstrated in minority populations and those with low levels of education and computer skills [42-45]. Tailoring interventions to enhance racial and ethnic relevance enhances interventions’ effects for blacks [46,47] and Hispanics [48]. Other authors, including those who created national guidelines for the US Department of Health and Human Service’s *Healthy People 2020* and from the US Centers for Disease Control, stress the need to deliver materials that are matched to patients’ levels of health literacy [49-51]. Brouwer [52] noted that greater personal relevance may be related to increased likelihood of successful dissemination of computer-delivered health care interventions. Jerant et al [43] summarized research on computer-tailored health interventions and concluded that these interventions are a, “highly promising” strategy for reducing health disparities. Individualization of information and teaching strategies can be undertaken in small groups by skilled educators, but it is not clear how the health care system would find the number of educators needed or how they would be paid. Computer-based interventions can provide similar tailoring to larger numbers of patients at lower costs [39,43].

### Expected Outcomes of a Chronic Disease Self-Management Health Literacy Intervention

Effects of a successful health literacy intervention targeting CDSM are likely to go beyond improved knowledge and skills. Francis et al [53] showed, for example, that improving low-literacy patients’ reading skills also had a positive impact on their mood, and a study completed by our group showed that an intervention to improve health literacy in persons treated for HIV had a modestly positive (but nonsignificant) effect on control beliefs [29]. Hibbard et al [54] showed that an intervention to develop chronic disease management skills was associated with increases in patient activation, and Lorig et al [55] showed changes in patient self-efficacy for managing their health conditions after a chronic disease management program. During the evaluation of a health literacy intervention for CDSM, it will be important to measure not only health literacy as a specific outcome, but also to assess the effects of the intervention on other health care-related variables, including activation and utilization. In this study, we will also evaluate the effects of the intervention on problems that span across diseases, such as pain, sleep, stress, depression, and treatment adherence [56].

### Study Objectives

In a previous study, Fostering Literacy for Good Health Today/Vive Desarollando Amplia Salud (FLIGHT/VIDAS), we developed a new measure of health literacy [25]. The new measure was validated with respect to other measures of health literacy as well as health-related quality of life [27]. Data from the study were then used to posit and test the ASK model of health literacy, which could be directly linked to improved health literacy [26]. In the proposed study, we will adapt and deploy the FLIGHT/VIDAS health literacy measure on tablet computers (Aim 1, see below), use it to evaluate a participant’s health literacy, and feed this information forward to tailor the CDSM health literacy intervention to a level of health literacy that is appropriate for each participant. Data from the study will also be used to further explore the paths among race, ethnicity, age, health literacy, and health.

Although it has been shown that computer-delivered tailored information interventions may be effective in improving health literacy in specific patient groups [28,29,43,44,57], it is not clear whether the same sort of computer-delivered, multimedia, and interactive approach will be effective in improving CDSM-related health literacy skills in persons with low baseline levels of health literacy. If the strategy is effective, it is also not clear whether effects will extend beyond health literacy and target symptoms (eg, depression, pain, or adherence) to quality of life, self-efficacy, and patient activation. The effects of this intervention will be compared to an active control group consisting of a similar intervention presented without tailoring, and each group will be examined for effects on health literacy, health status, health self-efficacy, patient activation, and treatment adherence.

In addition to the overall goal of assessing the usefulness of a tablet-delivered app, this study will further several other project-related goals, including the ongoing development of the FLIGHT/VIDAS health literacy measure in its tablet adaptation. The utility of alternate forms of the measure and their sensitivity to intervention effects will be evaluated, and a final goal of the study is to use these data to explore the complex relationships among race, ethnicity, health literacy, and health status.

### Aims and Hypotheses

In Aim 1 we will adapt and evaluate the tablet computer-administered measure of health literacy developed during an earlier study with African-American, Hispanic, and white non-Hispanic individuals 40 years of age and older, which operated on tablet computers. The two hypotheses of Aim 1 are: (*Hypothesis 1*) alternate forms of the new health literacy measure’s general health literacy and numeracy scales will be sensitive to intervention effects, showing improvements after participants complete the intervention; and (*Hypothesis 2*) the new health literacy measure will be acceptable, usable, and valid when administered on tablet computers.

In Aim 2 we will use the computer-administered measure to assign participants to a racially- and ethnically-tailored intervention that is delivered in a way that is appropriate to their level of health literacy. The two hypotheses of Aim 2 are: (*Hypothesis 3*) an interactive multimedia intervention will be more effective in improving health literacy, self-reported health, patient activation, health self-efficacy, and treatment adherence compared to a matched active control intervention; and (*Hypothesis 4*) the interactive multimedia intervention tailored to participants’ characteristics will significantly reduce health literacy differences between white non-Hispanics, African-Americans, and Hispanics.

In Aim 3 we will assess mediators and moderators of the relation of health literacy to race and ethnicity. We will also explore how these mediators and moderators are linked to health behaviors and actual health outcomes. The two hypotheses of Aim 2 are: (*Hypothesis 5*) health literacy will mediate relations between age, race and ethnicity, socioeconomic status, cognition, academic skills, and health status; and (*Hypothesis 6*) health literacy will moderate response to the health literacy intervention, with blacks and Hispanics with lower initial levels showing a greater response to the intervention than white non-Hispanics with higher levels of health literacy.

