#### Measures

Primary outcome measures will be health literacy (FLIGHT/VIDAS), self-reported general health (Medical Outcomes Study 36-item Short Form; SF-36 [95]), health self-efficacy (Chronic Disease Self-Efficacy Scale [96]), patient activation (Patient Activation Measure [97]), and treatment adherence. Additional data will provide the ability to consider race, ethnicity, age, and other variables as potential confounders. These data will include demographic variables, mood [98], stress [99], patient-provider relationships [100], treatment engagement, general cognitive abilities, academic skills, health conditions, current symptoms, health care attitudes, self-efficacy [101], and health care utilization.

Severity and number of health conditions will be assessed with the Functional Comorbidity Index [90], a previously validated measure linked to physical status, and an index based on the Midlife in the United States study [102] protocol, as used in our earlier study [27], to allow comparisons with data from that study. Assessments will include information on the specific symptoms of key problems in chronic disease management, and will allow a pre/postevaluation of the effects of the intervention on each. Simple measures of physical status (walking speed [103], body mass index [104], and waist-hip ratio [105]) will also be obtained to assess the effects of health literacy, cognition, and comorbidity on these variables, as they have all been related to risks for mortality [6,106,107].

Most self-report instruments will be administered via Automated Computer-Assisted Self-Interview (ACASI) software with assessment materials presented on touchscreen computers. This strategy enhances data collection by allowing participants anonymity in their responses and reduces issues with hand scoring of measures and manual data entry. Both sites will use the ACASI software Questionnaire Development System (QDS; Nova Research, Bethesda, Maryland). Individually administered measures, including assessments of cognitive, academic, and health literacy status, will be hand scored and verified. QDS output files will be transferred between sites using encrypted file transfer technology also available in REDCap.

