*Hypotheses 3* and *4* for this aim, related to the effects of the intervention on outcomes, will also be evaluated in mixed-effects regression models including relevant covariates, with separate models assessing each dependent variable (HL and NUM scales, SF-36 General Health, Chronic Disease Self-Efficacy Scale, Patient Activation Measure, and treatment adherence) providing the ability to evaluate between-groups differences and the interaction of group membership (each racial/ethnic group). Estimated marginal means for mixed-effects models will be compared across levels of effects. Exploratory analyses will evaluate the effect of the intervention on other outcomes, such as patient-provider relationships, treatment engagement, and health care service utilization. Exploratory analyses will evaluate the impact of age on these outcomes. Similar analyses will evaluate the effect of the intervention on specific conditions, such as pain, sleep, and fatigue.

##### Aim 3

*Hypotheses 5* and *6* for this aim, related to the significance of effects of race, cognition, socioeconomic status, and academic skills on health status and utilities (as mediated by health literacy) will be tested using structural models developed in the MPlus statistical software. The significance of indirect (mediating) effects will be tested using bias-corrected bootstrapped estimates. *Hypothesis 6*, which suggests that levels of health literacy will moderate the effects of the intervention, will be tested by creating an interaction variable and including it in the structural model for *Hypothesis 5*.

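### Hypothesis 6 varies race/ethnicity and initial literacy together, and no described model names both interactions with arm, so a racial/ethnic difference in benefit could partly be credited to literacy

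*Protocol article*

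**What the plan says.** All references are to the protocol article.

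- **Aims and Hypotheses, Aim 3.** Hypothesis 6 is a claim about health literacy as moderator. Its expected pattern is "with blacks and Hispanics with lower initial levels showing a greater response to the intervention than white non-Hispanics with higher levels of health literacy".
- **Low Health Literacy and Disparities.** Under Aim 3 the authors also announce that "we will assess the potential moderating effect of race, ethnicity, and age in response to an intervention to improve health literacy". The same section reports that literacy differs by group: "Twenty-four percent of blacks (9.5 million persons), 41% of Hispanics (21 million persons") have below-basic levels. It gives no percentage for white non-Hispanics.
- **Study Hypotheses, Aim 3.** Hypothesis 6 "will be tested by creating an interaction variable and including it in the structural model for" Hypothesis 5. That structural model is described as "related to the significance of effects of race, cognition, socioeconomic status, and academic skills on health status and utilities (as mediated by health literacy"). Race is therefore in it as a predictor; an interaction of race with arm is not named.
- **Study Hypotheses, Aim 2.** Separate mixed-effects models, with covariates not listed, give "the ability to evaluate between-groups differences and the interaction of group membership (each racial/ethnic group"). An interaction of baseline literacy with arm is not named there.
- **Interventions (Phase 2).** The experimental modules are tailored on language, literacy level and racial or ethnic relevance. The control materials are at one reading level and carry no racial or ethnic tailoring.

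**The concern.** The predicted pattern sets one group against another that differs from it in two respects. If literacy had no influence on benefit and race/ethnicity did, the pattern would still appear, so seeing it says nothing about which factor is at work.

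The described test should separate the two, but as written it may not. Both factors can plausibly change the benefit because the experimental arm is built around both, and the two are correlated in the population. When only one of two correlated moderators has its interaction with arm in the model, that term absorbs part of the other. If black and Hispanic participants gain more and start with lower literacy, the error runs in the direction that confirms Hypothesis 6. The reverse error can occur in the Aim 2 models, where a literacy effect can appear as a racial/ethnic one.

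The two readings lead to different uses of the result: aim the intervention at people by literacy level, or by group.

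**Working it through.** **Sample size.** The Power Analyses section crosses three literacy/control levels with three racial/ethnic groups and wants 30 per group after up to 38% attrition. Read as 9 cells, 432 / 9 = 48 per cell and 1 − 30/48 = 37.5%, so the stated 432 is reproduced. After 38% loss, 432 × 0.62 = 267.84, about 268. The check below uses n = 268 and n = 432. The stated powers cannot be reproduced because no effect size is given.

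**Assumed inputs (not in the documents).**
- True literacy-by-arm effect: zero.
- Extra benefit in black and Hispanic participants, *g*: 0.3 to 0.5 SD.
- Baseline literacy gap, *d*: 0, 0.5 or 0.8 within-group SD.
- Black and Hispanic share, *p*: 2/3 (from three equal racial/ethnic groups), so *p*(1−*p*) = 0.222.
- Residual SD, *s*: 0.85 to 1. Allocation 1:1, two-sided 5% level.

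**Bias when race enters as a main effect only.** By randomisation, the race main effect is uncorrelated with the arm interaction and cannot absorb it. The literacy-by-arm slope takes up *g* times the regression of group on literacy:

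bias = −*g* × *d* × 0.222 / (1 + 0.222*d*²)

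Standard error ≈ 2*s* / √(*n*(1 + 0.222*d*²)). The false-positive rate is P(|Z + bias/SE| > 1.96).

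| Gap *d* | *g* | *n* | *s* | bias | SE | false positives |
|---|---|---|---|---|---|---|
| 0 | any | any | any | 0 | – | 5% |
| 0.5 | 0.3 | 268 | 1 | −0.032 | 0.119 | 5.8% |
| 0.5 | 0.5 | 432 | 0.85 | −0.053 | 0.080 | 10.1% |
| 0.8 | 0.3 | 268 | 1 | −0.047 | 0.114 | 6.9% |
| 0.8 | 0.5 | 432 | 0.85 | −0.078 | 0.077 | 17.4% |

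The rows at each gap are the mildest and the most severe corner. A negative slope means more benefit at lower literacy, the direction Hypothesis 6 predicts.

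**Simulation.** Simulated trials agree with these formulas to within about one percentage point. With 270 completers and residual SD 1, the rate was 5% at a gap of 0 or 0.3 SD, 6 to 7% at 0.5 SD and 7 to 10% at 0.8 SD. Dropping or keeping the race main effect made practically no difference (for example, bias −0.076 against −0.077). Adding race-by-arm brought the bias to about 0 and the rate to 4 to 6%. An allocation of two thirds to the active arm gave nearly the same picture as 1:1.

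**Price of the joint model.** The standard error of the literacy term rises by √(1 + 0.222*d*²): √1.0556 = 1.03 at a 0.5 SD gap and √1.142 = 1.07 at 0.8 SD. In the simulations the rise was about 2 to 7%.

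**The reverse error.** If only literacy moderates, a race-by-arm term fitted without literacy-by-arm shows a spurious group difference equal to the gap times the literacy slope.

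**The case against.** The strongest reply is that the article is a condensed account. It mentions an interaction variable and relevant covariates, lists no full model and excludes no term. Full model specifications usually sit in a statistical analysis plan, which is not shown. This stands as far as it goes: one cannot say that the joint model will not be fitted. But the hypothesis itself is worded in a way that mixes the two factors, and the described test, taken at its word, does not undo this.

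The Power Analyses section lists literacy level and race/ethnicity side by side, claims adequate power for two-way interactions and promises to look at higher-level ones. That does not settle the matter. Its literacy factor is high, low and control, with control not split by literacy, so it does not yield a literacy-by-arm interaction. The Measures section says "Additional data will provide the ability to consider race, ethnicity, age, and other variables as potential confounders", but does not tie this to the moderation test.

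A reader might infer three stronger things that the documents do not support:

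- **That each moderator is tested with the other absent from the model.** Race is in the Hypothesis 5 model, and the Aim 2 covariates are unnamed, so baseline literacy may be among them. What is not named is the second interaction with arm.
- **That Hypothesis 6 has a false-positive rate of 18 to 64%.** Those figures describe a direct comparison of benefit in low-literacy minority participants and high-literacy whites. The article predicts that pattern but does not describe it as the test; the analysis section restates Hypothesis 6 in terms of literacy alone.
- **That racial/ethnic moderation is promised and then dropped.** It is covered in the Aim 2 models, though not in the Aim 3 analysis where the Introduction places it.

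It is also fair to say that enrolment is restricted to low health literacy, which tends to narrow the gap between groups and with it the bias.

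**Conclusion.** The concern holds in a limited form. Hypothesis 6 makes a literacy claim through a contrast that also changes race/ethnicity, and no described model names both interactions with arm. For the test as described, the excess of false positives is modest: none if the groups do not differ in baseline literacy, about 6 to 10% at a 0.5 SD gap and 7 to 17% at 0.8 SD, against a nominal 5%. The upper figure needs the largest assumed gap, the largest assumed race-by-arm effect, the smaller residual SD and full retention of 432. The documents give neither the gap within the eligible range nor a race-by-arm effect, so the actual size is unknown. The point concerns an Aim 3 moderation analysis and does not affect the randomised comparison of arms in Hypothesis 3. It should be changed because the improvement is cheap and the answer bears on whom the intervention is for.

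**What to change.** 1. In the Hypothesis 6 model, include baseline-literacy-by-arm and race/ethnicity-by-arm terms together, each with its main effect.
2. Judge Hypothesis 6 on the literacy-by-arm term in that model, and report moderation by race/ethnicity from its own term. This also delivers the racial/ethnic moderation that the Introduction places under Aim 3.
3. Reword Hypothesis 6, for example: *lower initial health literacy predicts a larger benefit over control, adjusting for racial/ethnic differences in benefit*. Do not offer the contrast of lower-literacy minority participants with higher-literacy whites as evidence for literacy moderation.

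The cost is the added race/ethnicity-by-arm terms, one reworded sentence and a standard error for the literacy interaction about 2 to 7% larger at the gaps assumed. No new data are needed.
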